### **Assessments:**

Assessments will be performed regularly throughout the duration of the trial according to the flow charts ([Table 2-1](#) and [Table 2-2](#)), and Section [8](#), Methods and Assessments, and the following data will be evaluated:

Primary assessment:

- Safety and tolerability

Secondary assessments:

- Efficacy (primary assessment for the MD expansion phase)
- Pharmacokinetics
- Pharmacodynamics
- Pharmacogenomics
- Immunogenicity

**Trial products:**

The active drug product, Anti-IL-20 (109-0012) 100 mg/vial, will be provided as freeze dried powder, which will be reconstituted with sterile water for injection to a concentration of 100 mg/mL. For the lowest doses the 100 mg/mL solution will be diluted to 10 or 1 mg/mL. The placebo solution, Placebo (109-0012) 0 mg/mL, will be provided as liquid. The placebo solution will also be used as diluent for the reconstituted active drug product. The freeze dried powder as well as the placebo solution should be kept at 2-8 °C. Both the trial drug and the placebo formulation will be administered subcutaneously, using standard syringes. Anti-IL-20 (109-0012) 100 mg/vial will be administered at the following doses (see also [Table 5-2](#)):

Single dose, dose-escalation phase: 0.01, 0.05, 0.20, 0.6, 1.5 and 3.0.

Multiple dose, dose-escalation phase: 0.05, 0.20, 0.5, 1.0 and 2.0.

| Visit number                        | 1            | 2   | 3 | 4 | 5  | 6   | 7   | 8   | 9   | 10  | 11  |
|-------------------------------------|--------------|-----|---|---|----|-----|-----------------|-----|-----------------|-----|-----|
| Timing: weeks                       | 0            | 1   |   | 2 | 3  | 5   | 7               | 9   | 11              | 13  | 16  |
| Timing: days                        | 0            | 1-2 | 3 | 8 | 15 | 29  | 43  | 57  | 71  | 85  | 106 |
| Window: days                        | -21
to -4 |     |   |   |    | ± 3 | ± 3             | ± 3 | ± 3             | ± 3 | ± 3 |
| Subject related
info/assessments |              |     |   |   |    |     |                 |     |                 |     |     |
| Informed consent                    | x            |     |   |   |    |     |                 |     |                 |     |     |
| Administration of trial product     |              | x   |   |   |    |     |                 |     |                 |     |     |

: Only telephone contact, no visit at site.

: Including known history of human immunodeficiency virus (HIV).

: Weight only.

: PK sampling of 109-0012 will occur prior to dosing (0 hours) and at 2, 4, 8, 10 and 24 hours after drug administration.

: Assessments will be performed prior to dosing on day 1, and 24 hours post-dosing.

: Sampling will occur prior to dosing (0 hours).

: Sampling will occur prior to dosing (0 hours) and 24 hours post-dosing.

: Including follicle stimulating hormone (FSH), if applicable, at screening.

: Electrocardiogram (ECG) will be recorded prior to dosing (0 hours) and at 2, 8 and 24 hours after drug administration.

: Blood pressure will be measured prior to dosing (0 hours) and at 1, 2, 4, 8 and 24 hours after drug administration.

: Serum and plasma samples will be collected prior to dosing (0 hours) on day 1, and at 10 hours and 24 hours post-dosing. Serum aliquots will be used for IL-20 and sCD25 analyses. Serum and plasma aliquots will be stored for further analyses, e.g. by multianalyte profiling.

: Whole blood samples for gene expression (microarray and qRT-PCR) analyses will be collected prior to dosing (0 hours) on day 1 and 24 hours post-dosing.

**Table 2-2      Flow chart for multiple dose, dose-escalation, and expansion phases**

[illegible]

| Visit number                     | 1         | 2               | 3 | 4 | 5               | 6  | 7                  | 8   | 9   | 10  | 11  | 12  |
|----------------------------------|-----------|-----------------|---|---|-----------------|----|--------------------|-----|-----|-----|-----|-----|
| Timing: weeks                    | 0         | 1               |   | 2 | 3               | 5  | 7                  | 9   | 11  | 15  | 19  | 22  |
| Timing: days                     | 0         | 1               | 2 | 3 | 15              | 29 | 43-44  | 57  | 71  | 99  | 127 | 148 |
| Window: days                     | -21 to -4 |                 |   |   |                 |    |                    | ± 3 | ± 3 | ± 3 | ± 3 | ± 3 |
| Subject related info/assessments |           |                 |   |   |                 |    |                    |     |     |     |     |     |
| Informed consent                 | x         |                 |   |   |                 |    |                    |     |     |     |     |     |
| Molecular biomarkers             |           | x  | x | x | x  |    |                    |     |     |     |     |     |
| Trial material                   |           |                 |   |   |                 |    |                    |     |     |     |     |     |
| IVRS call                        | x         | x               |   |   | x               | x  | x                  |     |     |     |     |     |
| Drug accountability              |           | x               |   |   | x               | x  | x                  |     |     |     |     |     |
| Administration of trial product  |           | x               |   |   | x               | x  | x                  |     |     |     |     |     |

: A 24-hour PK sample after last drug administration should be collected at day 44 (no other assessments will be performed).

: Including known history of HIV.

: Weight only.

: PK sampling of 109-0012 will be performed prior to dosing (0 hours) and at 1, 2, 4 and 24 hours after first and last drug administration.

: Blood sampling for PK measurement of 109-0012 will be performed prior to drug administration (0 hours) in order to obtain a trough value.

: Assessments will be performed prior to dosing.

: Sampling will occur prior to dosing (0 hours).

: Including FSH (if applicable) at screening.

: Subjects must be fasting from midnight the same day until blood sampling.

: ECG will be recorded prior to dosing (0 hours) and at 2 and 4 hours after dosing.

: Blood pressure will be measured prior to dosing (0 hours) and at 1, 2 and 4 hours after dosing.

: Serum and plasma samples will be collected prior to dosing (0 hours). Serum aliquots will be used for IL-20 and sCD25 analyses. Serum and plasma aliquots will be stored for further analyses, e.g. by multianalyte profiling

: Only for MD expansion phase.

: Lesional biopsies (1x6 mm) will be collected at Day 2, 15 and 99. At Day 2 and Day 15 this will occur prior to dosing (0 hours).

: Non-lesional biopsy (1x3 mm) will be collected only at baseline.

: Whole blood samples for gene expression (microarray and qRT-PCR) analyses will be collected prior to dosing (0 hours).

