## 7 Trial schedule

If consent is obtained and subjects are considered eligible they will be scheduled for a dosing visit, which is set to trial Day 1 for each subject, within 4 to 21 days after the screening visit.

There will be a recruitment period of approximately three weeks before each new cohort. A pre-screening contact can be established where subjects are informed about the trial and the criteria for participation.

Planned first trial site ready: 1 April 2008

Planned date for first patient first visit (FPFV): 7 April 2008

Planned completion of the last patient: November 2010

The end of the clinical trial is defined as the last visit of the last patient.

Planned completion of clinical trial report: April 2011

This trial is subject to registration before subject enrolment according to the specifications from the International Committee of Medical Journal Editors (ICMJE) . Novo Nordisk will ensure the trial is registered at ClinicalTrials.gov according to the requirements from the Food and Drug Administration (FDA)  and ICMJE .

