3. ECG
4. BSA
5. PGA
6. Haematology
7. Biochemistry
8. Urinalysis
9. Hormones
10. Lipids
11. PASI and VAS (if applicable)
12. Sampling for molecular biomarkers (baseline)
13. Sampling for serum/plasma biomarkers (baseline)
14. Sampling for antibodies (baseline)
15. Lesional skin biopsies (1x6 mm to be split for histopathology+IHC and array/qRT-PCR analyses) and non-lesional skin biopsies (1x3 mm for baseline histopathology+IHC). This procedure is optional.
16. Urine pregnancy test (if applicable)
17. Inclusion and exclusion criteria
18. Concomitant medication
19. Adverse events
20. PK sample (0 hours)

Thereafter subjects will be randomised **by IVRS** and receive a subcutaneous injection of either active treatment or placebo into the abdomen. Since the trial is double-blind, neither the subject nor the investigator/study nurse will know whether active treatment or placebo is administered. There is a 3:1 chance of receiving active treatment.

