**Samplings and recordings occurring after trial product administration:**

1. ECG will be recorded at 2 and 4 hours after each drug administration.
2. Blood pressure will be measured at 2 and 4 hours after each drug administration.
3. After each drug administration subjects will be closely monitored during their 4-hour-stay.
4. Drug accountability will be performed via **IVRS**.

Day 15: Sampling for molecular biomarkers and lesional skin biopsies (1x6 mm to be split in half). The skin biopsy procedure is optional.

Day 43: Sampling for antibodies.

Subjects are allowed to leave the site 4 hours after drug administration when all samples have been collected and all assessments have been recorded.

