### **Samplings and recordings occurring after trial product administration:**

1. ECG will be recorded at 2 and 4 hours after each drug administration.
2. Blood pressure will be measured at 2 and 4 hours after each drug administration.
3. After each drug administration subjects will be closely monitored during their 4-hour-stay.
4. Drug accountability will be performed via **IVRS**.

Day 15: Sampling for molecular biomarkers, lesional skin biopsies (1x6 mm to be split in half). The skin biopsy procedure is optional.

Day 43: Sampling for antibodies.

Subjects are allowed to leave the site 4 hours after drug administration when all samples have been collected and all assessments have been recorded.

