#### **Skin biopsies**

Hyper proliferation of keratinocytes and epidermal infiltration with both T cells and dendritic cells are hallmarks of psoriasis and  $CD68^+/CD11^+$  myeloid cells have been suggested to be an important source of IL-20. In addition to keratinocytosis and leukocyte infiltration, increased angiogenesis is an early prominent event in psoriasis. In order to search for morphological markers of 109-0012 effects, skin biopsies will be collected and subjected to histopathological and immunohistochemical analyses. Lesional biopsies (1x6 mm), obtained from the centre of the lesion, will be collected at baseline and at trial Week 3 and trial Week 15. Each biopsy will be split into two equal halves (1x3 mm) and subjected to cryo preservation. Furthermore, a non-lesional biopsy (1x3 mm, cryo

preservation) will be collected, but only at baseline. The assessments (for the non-lesional and one of the half lesional biopsies) may include but will not be limited to:

- Histopathological scoring including assessment of epidermal thickness and proliferation, e.g. by H&E, keratin 16, and Ki67 stain
- Exploratory assessment of 109-0012 effects on skin, vasculature, and immune system:
  - expression of IL-20 and IL-20 receptors
  - infiltrating leukocyte subsets, e.g. CD3, CD11c, and CD68
  - IL-20 signalling, e.g. pSTAT3
  - angiogenesis, e.g. CD31 stain

Results from skin biopsy analyses will be analysed at a later time point and reported separately and appended to the clinical trial report.

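### The MD-phase sampling schedule contradicts itself on the first lesional biopsy (Day 1 or Day 2) and on whether the Day 15 biopsy and gene-expression blood come before or after dosing

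*Protocol*

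**What the plan says.** Table 2-2 covers both MD phases (dose-escalation and expansion). Footnote 14 reads "Lesional biopsies (1x6 mm) will be collected at Day 2, 15 and 99" and continues "At Day 2 and Day 15 this will occur prior to dosing (0 hours". Footnote 16 reads "Whole blood samples for gene expression (microarray and qRT-PCR) analyses will be collected prior to dosing (0 hours"; in the molecular biomarkers row it is attached to the Day 1 and Day 15 visits.

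The dosing days are stated consistently. Section 7 says of eligible subjects that "they will be scheduled for a dosing visit, which is set to trial Day 1 for each subject". Section 5.2 puts the later doses on Days 15, 29 and 43, and Table 2-2 marks administration at the same four visits.

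Sections 8.1.2 and 8.1.3 include, in the Day 1 list to be completed before administration, "Lesional skin biopsies (1x6 mm to be split for histopathology+IHC and array/qRT-PCR analyses". Section 8.4.2 says that lesional biopsies "will be collected at baseline and at trial Week 3 and trial Week 15"; Sections 8.4.3 and 8.4.5.6 give the same schedule.

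For Day 15, below the heading for samples taken after administration, Section 8.1.2 has "Day 15: Sampling for molecular biomarkers and lesional skin biopsies (1x6 mm to be split in half" and Section 8.1.3 has "Day 15: Sampling for molecular biomarkers, lesional skin biopsies (1x6 mm to be split in half". Both sections state that the biopsy is optional.

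**The concern.** The skin and molecular biomarkers serve a stated secondary objective of the MD phases. Section 4.2 lists histopathology, IL-20 signalling and skin gene expression as expansion-phase endpoints, and Section 17.5 names skin histology as a possible input to the PK/PD model. Change in a lesion is interpretable only if the first biopsy precedes treatment and later biopsies are timed alike at all sites.

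Section 6.1 foresees 5 to 10 sites, with a single site for the SD phase. The MD phases therefore involve several sites, and these may resolve a contradictory instruction differently. A baseline biopsy taken after the first dose cannot be replaced. A mixture of pre- and post-dose samples on Day 15 would add a timing difference that could follow site.

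**Working it through.** The plan gives no figure to reproduce. The check is a comparison of the texts, followed by a count and an illustration of exposure.

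**1. First lesional biopsy**

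| Source | Day | Relation to dose |
|---|---|---|
| Table 2-2, footnote 14 | Day 2 | before dosing, 0 hours |
| Sections 8.1.2 and 8.1.3, Day 1 | Day 1 | before administration |
| Sections 8.1.2 and 8.1.3, Days 2 and 3 | no biopsy listed | not applicable |
| Sections 8.4.2, 8.4.3, 8.4.5.6 | baseline | not stated further |

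Doses fall on Days 1, 15, 29 and 43, so Day 2 is 2 − 1 = 1 day after the first dose. Sections 8.1.2 and 8.1.3 themselves label Day 2 as the 24-hour PK time. Footnote 14 therefore cannot be carried out as written.

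Its other two biopsies match Section 8.4. With week = (day − 1)/7 + 1, Day 15 is 14/7 + 1 = week 3 and Day 99 is 98/7 + 1 = week 15. By elimination, the Day 2 biopsy is the one that Section 8.4 calls baseline.

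**2. Day 15 biopsy and gene-expression blood**

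| Source | Relation to the second dose |
|---|---|
| Footnote 14 (biopsy) | before |
| Footnote 16 (blood) | before |
| Sections 8.1.2 and 8.1.3, numbered pre-dose list | neither sample appears |
| Sections 8.1.2 and 8.1.3, post-administration heading | both samples appear |

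The conflict is the same in both MD phases.

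**3. How many subjects**

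From Section 5.1, MD dose-escalation has 15 active + 5 placebo = 20 and expansion has 26 active + 13 placebo = 39. The total is 59, of whom 5 + 13 = 18 receive placebo. Subjects who could have a drug-exposed baseline biopsy: 15 + 26 = 41. Refusals of the optional biopsy lower this; replacements or added cohorts would raise it.

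**4. What Day 2 means in exposure (illustration)**

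The half-life of 15 to 20 days is from Section 5.3. The first-order absorption rate ka is an assumption, taken as 0.2 to 1.0 per day. For one compartment with ke = ln 2 / half-life, up to a constant factor:

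C(t) = ka/(ka − ke) × [exp(−ke·t) − exp(−ka·t)], peak at t = ln(ka/ke)/(ka − ke).

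| ka per day | C(1 day)/peak, half-life 15 d | Half-life 20 d |
|---|---|---|
| 0.2 | 0.177/0.644 = 27% | 26% |
| 0.5 | 0.384/0.785 = 49% | 47% |
| 1.0 | 0.615/0.862 = 71% | 70% |

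A Day 2 biopsy would thus see a substantial part of the first-dose peak.

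**5. What a late Day 15 sample means**

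Subjects may leave 4 hours after the second dose. In the same model, the rise over the pre-dose level is [C(14 d + 4 h) + C(4 h)]/C(14 d) − 1.

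- Half-life 15 days, ka 0.2: (0.599 + 0.033)/0.602 − 1 = 5%.
- Half-life 15 days, ka 1.0: (0.545 + 0.153)/0.549 − 1 = 27%.
- Half-life 20 days: 5% to 23%.

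The Day 15 effect on exposure is much smaller than the Day 2 effect.

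**The case against.** The best defence is that the intended schedule can be recovered. Footnote 14 itself says the biopsy precedes dosing, which rules out a sample 24 hours after the dose. Day 2 may be a slip for Visit 2, which is Day 1, although the Protocol does not say so. Every other text keeps the baseline biopsy before treatment. This narrows the risk to a site that works from the printed day, but does not remove it: the wrong day is printed twice, in the flow chart for both MD phases.

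On Day 15, the post-dose reading rests on the heading alone. The lines are unnumbered additions without a clock time, whereas the footnotes state the timing outright. That is fair, but the same samples are also absent from the pre-dose list.

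Section 8.1.4 already requires exact sampling times for serum, blood and plasma, so a late Day 15 blood sample could be identified. It does not name tissue, and the biopsy label in Section 8.4.5.6 carries a visit number but no time.

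A reader might infer several stronger points that the documents do not support:

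- **That following either text loses the pre-dose baseline.** Each text endangers a different sample. Section 8.1 keeps the baseline biopsy before dosing, and the baseline gene-expression blood is pre-dose in both texts.
- **That Day 15 loses a pre-treatment sample.** It falls two weeks after the first dose and is on treatment either way.
- **That all 59 MD subjects could have an exposed baseline.** Eighteen receive placebo.
- **That the Day 43 antibody sample is also misplaced.** It is listed after dosing, but no legible text requires it earlier.

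**Conclusion.** The point holds as an internal inconsistency in two places: the day of the first lesional biopsy, and the pre- or post-dose timing of the Day 15 biopsy and gene-expression blood. It is wrong as written but minor, and it is not a questionable design choice, since the intended pre-dose baseline is clear from most of the text.

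The first conflict matters more. It could expose the baseline biopsy to drug in at most 41 active subjects under the planned cohort sizes, at an illustrative 26% to 71% of the first-dose peak. Skin-biopsy endpoints are listed in Section 4.2 only for the expansion phase, where 26 subjects are active. The second conflict threatens consistency of timing across sites more than the meaning of the sample.

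The exposure percentages rest on the assumed absorption rates and a one-compartment model; the contradictions do not. The biopsy row of Table 2-2 is not legible in the text at hand, so the flow-chart side rests on its footnotes. PASI75, the toxicity endpoint, dose escalation and the sample size are unaffected.

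**What to change.** 1. In Table 2-2, footnote 14, replace Day 2 by Day 1 (Visit 2) in both places, to agree with Sections 8.1.2, 8.1.3 and 8.4.
2. In Sections 8.1.2 and 8.1.3, move the Day 15 biopsy and molecular biomarker sample from the post-administration block to the pre-dose list, to agree with footnotes 14 and 16.
3. In Section 8.1.4, add tissue to the samples whose exact collection time is recorded, so that a mistimed biopsy can be identified at analysis.

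Leave the Day 43 antibody listing as it is.

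The cost is one footnote, two lists and one time field in the eCRF, with no added visit, sample or procedure.

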## 3 Introduction

In this document the Principal Investigator will be referred to as the Investigator.

### 3.1 Basic information

#### 3.1.1 Psoriasis

Psoriasis is a T-cell mediated inflammatory disease where the activation of the immune system, via cytokines, results in epidermal hyperplasia, hyperproliferation of keratinocytes and cutaneous infiltration by granulocytes.

It is a serious, chronic disease, characterised by thickened erythematous plaques, usually located on elbows, knees, scalp, lower back, face, palms, and soles of the feet. Psoriasis is associated with significant co-morbidity (obesity, cardiovascular morbidity) and with negative influence on the quality of life.

The prevalence of psoriasis is 1-3% and the mean age of onset is 28 years. Among different types, plaque psoriasis is the most common type, accounting for > 80% of subjects, and men and women are equally affected. Furthermore, 10-30% of subjects with psoriasis suffer from joint pain or arthritis. There is currently no cure for psoriasis, which affects about 125 million people worldwide. Approximately 25% of all patients experience moderate-to-severe disease symptoms.

The aetiology of psoriasis is unknown, but genetic factors can determine the predisposition, while stress, skin injuries, infections, certain medications and sunburn can trigger the development of psoriasis. T lymphocytes, especially CD8+ and CD4+ cells, are involved in the mediation of the disease. CD8+ and CD4+ cells produce TH1 cytokines, of which mainly interferon  $\gamma$  (IFN $\gamma$ ), interleukin-2 (IL-2) and tumour necrosis factor  $\alpha$  (TNF $\alpha$ ) play important roles for the pathogenesis of psoriasis. Furthermore, TNF $\alpha$  stimulates the production of other inflammatory cytokines and promotes angiogenesis, also observed in psoriasis. The initiation of psoriasis by T-cells is a complex process, and T-cells must first become activated before they can migrate to the skin and start secreting cytokines. Moreover, serum levels of sCD25 (soluble form of the IL-2 $\alpha$  receptor) which is secreted from T cells upon activation, has been shown to correlate to the PASI score during treatment.

#### 3.1.2 Existing treatment

There exists no permanent cure for psoriasis, and the available treatments aim at improving the quality of life for the subjects, and to reduce the extent and severity of the disease. The treatment depends mainly on the severity of the disease, but also on local practice. Topical treatment is primarily recommended for mild psoriasis, and vitamin D-analogues, such as calcipotriol, are commonly used, alone or in combination with local corticosteroid treatment. Treatment of

moderate-to-severe psoriasis is often initiated with UVB (ultraviolet light B) radiation, or PUVA (UVA radiation together with systemic psoralene treatment). Systemic treatment for subjects with moderate to severe psoriasis, often involving arthritis, includes methotrexate (being the single most used systemic agent), cyclosporin and retinoids.

Monoclonal antibodies, mostly humanised, belong to the more recently developed treatments, commonly called biologics. Treatment with TNF $\alpha$ -inhibitors (etanercept, adalimumab and infliximab) and T-cell inhibitors (alefacept and efalizumab) has become more and more common, although still only constituting less than 5% of the total usage of systemic agents.

